## Materials and procedure

The study protocol includes two phases of assessment, spaced out with a rehabilitation period. Specifically, the assessment will be conducted at T0 (acute upon admission) and T1 (post-rehabilitation lasting 15 days for Parkinson’s patients and 4 weeks for patients with eating disorders). In each phase, we will collect data on neuropsychological performance, self-report questionnaires, psychophysiological measures, and neuroendocrine measures for participants with AN, as described in Fig 2. In some cases, the tests for the two populations will be different, for example, in PD patients the administration of the tests could be leaner and faster (Fig 2).

**Fig 2 pone.0293921.g002:**
[figure not shown]
Structure of assessment.

The neuropsychological tests and self-report questionnaires will be administered to patients at their admission to acute care (administered by T0-T1, all with an Italian validation and adaptation). Following, the IAPS will be administered at both times T0 and time T1. Images with stimuli that are too salient in comparison to the disorders under study will be eliminated using the arousal-valence selection criteria (i.e. food for patients with an eating disorder). The order of administration will be planned and distributed randomly among the subjects. This set comprised 156 images, each lasting for a duration of 10 seconds. These images were grouped into 13 blocks, to cover 12 possible transitions between quadrants (Fig 3). Each block had 12 images, each containing combinations of varying arousal and valence levels. The IAPS images had standardized scores of Arousal and Valence, according to the 9-likert point of Self-Manikin assessment (SAM). We choose only images with those specificities: for high arousal/valence (>6 Likert point scores), and for low arousal/valence (<4 Likert point scores). Notably, each participant’s sequence of image presentation was randomized to minimize order effects.

**Fig 3 pone.0293921.g003:**
[figure not shown]
IAPS protocol. The IAPS protocol first involves careful selection of images consistent with the affective states quadrant (top part of the figure) and then implementation into a sequence consisting of 13 image blocks, resulting in 12 possible transitions for analysis. Emotional elicitation is then measured in physiological terms by f-EMG, GSR, ECG, RSP. The stimuli images shown are for illustration purposes only and are not the used ones that have been extracted from IAPS database.

Peripheral physiological parameters such as the ECG, BVP, GSR, EOG, RSP, and facial EMG (corrugator and zygomatic) will be detected throughout the test as measurable indicators of emotional arousal (T0-T1). Additionally, morning venous blood sampling is planned to analyse biohumoral parameters in subjects with eating disorders, including interleukin 6, cortisol, serotonin, catecholamines, and endorphins at T0 and T1.

PD patients and participants affected by AN will be recruited at the IRCCS Auxologico Piancavallo, at the Neurology and Neurorehabilitation Unit, and the Rehabilitation of eating disorder and Nutrition Unit respectively. Patients will receive all the information required to sign the informed consent form, and inclusion/exclusion criteria will be evaluated by a neurologist and an expert physician in eating disorders.

### Assessment

Patients received a complete behavioral and neuropsychological evaluation to assess flexibility, divide into three parts: (i) neuropsychological tests, (ii) self-report questionnaire, and (iii) IAPS administration. The assessment will be done in acute care (T0) and the same tests will be performed after a period of rehabilitation (T1). The battery includes the Trail Making Test **(TMT),** the Tower of London **(ToL),** the phonemic and semantic verbal fluency, the phonemic/semantic alternate fluency test, and the Modified Wisconsin Card Sorting Test **(WCST).** The TMT [84] comprised two parts: TMT-A and TMT-B. The first is a searching task, the second requires shifting abilities. The request is to connect the numbers from 1 to 25 in sequential order or numbers from 1 to 13 and letters from A to N in alternating order (i.e., 1, A, 2, B, etc.) respectively. The time used to perform each task is considered during the scoring: the highest the time the worst score. The ToL traditionally measures strategical reasoning, problem-solving, and mental planning. The task consists of moving tree beads to reproduce a target configuration; specifically, three abilities are required: (a) creating a general plan; (b) arranging beads into a series of movements; and (c) maintaining the general plan in working memory. Time and accuracy are evaluated [85]. Phonemic and verbal fluency enables a quick and effective assessment of lexical access and the breadth of semantic inventory, the ability to use research strategies in the lexicon, and spontaneous flexibility. In the phonemic part, patients are asked to report as many words as they can produce beginning with a certain letter of the alphabet (F, L, P); while, in the semantic part they are asked to report words belonging to a specific category (car brands, fruits, animals). Patients have a minute of time and the sum of the right items produced for each letter/category determines the final score. Moreover, the alternate fluency [86] is used to analyze set-shifting abilities. The task requires rapidly changing the mindset to generate words by continuously alternating between phonemic and semantic criteria. The WCST consists of sorting the cards; However, the sorting rule must be deduced based on the feedback (correct sorting or not). As soon as the rule is found, it is altered, and the task then finds a new sort rule. Perceptual criteria of the elements on the cards, such as color, shape, or number, are the basis for the sorting rules. The Modified Card Sorting Test consists of a set of stimulus and response cards. The first is composed of four cards each of which is unique in terms of color (red, green, blue, or yellow), shape (triangle, star, cross, or circle), and the number of items (one, two, three or four). The response cards consist of 2 sets of 24 cards comprising all possible combinations of the color, shape, and number attributes. The subject is instructed to place each response card below a stimulus card, deducing sorting rules based on the clinician’s feedback (right or wrong placement) [87].

Similarly to the neuropsychological assessment, both groups will also perform self-reports of cognitive flexibility with the following instruments: (i) Cognitive Flexibility Inventory **(CFI)** [88, 89], with 19 items, falls into two distinct subclasses: Alternatives (12 elements) and Control (7 elements). These items are rated on a 7-point Likert scale (1 being strongly disagreed with, and 7 being strongly agreed with. The highest results generally indicate high cognitive flexibility in the overall measure; (ii) Cognitive Control and Flexibility Questionnaire **(CCFQ)** [90] is a 18-item questionnaire that assesses a person’s perceived capacity to exert control over unwanted (negative) intrusive thoughts and emotions as well as their capacity to adapt to stressful circumstances; (iii) Cognitive Flexibility Scale **(CFS)** [91]: the questionnaire consists of 12 Items that evaluate the relational communication flexibility; (iv) Flexible Regulation of Emotional Expression **(FREE)** which assesses emotional regulation in terms of flexible management between negative and positive affective states and vice versa (16 items) [92].

Patients with AN will be also assessed with additional tests: (v) Detail and Flexible Questionnaire **(DFlex)** [93] is a self-report tool for assessing cognitive inflexibility, based on cognitive styles.

Finally, we will measure also concurrent constructs, significantly associated with flexibility:

(vi) State-Trait Anxiety Inventory-subscale Trait **(STAI Y2):** It is a questionnaire made up of 20 items on a Likert scale with a four-point scale that refers to the Trait Anxiety; (vii) Emotion Regulation Questionnaire **(ERQ- 10 item)** [94, 95] is a 10-item questionnaire with two scales representing two distinct methods of emotion regulation: cognitive reassessment (6 items) and expressive suppression (4 items). The questions focus on the subject’s emotional life, particularly his ability to control (i.e., regulate and manage) his emotions. The 10 items are scored using a 7-point Likert scale that ranges from strongly disagreeing to strongly agreeing; (viii) Beck Depression Inventory **(BDI)** is a self-evaluation tool with 21 multiple-choice questions about the subject’s depressive states; (ix) The Wong and Law Emotional Intelligence Scale **(WLEIS)** [96] is a measure of Emotional Intelligence of 16 items, based on the skill model of Mayer and Salovey. The scale measures four dimensions: Auto-Emotional Evaluation, Evaluation of Others’ Emotions, Use of Emotions, Regulation of Emotions; (x) Barratt Impulsiveness Scale **(BIS)** [97] is a widely used measure of impulsivity. It includes 30 elements that are evaluated to produce six first order factors (attention, motor, self-control, cognitive complexity, perseverance and impulsiveness of cognitive instability) and three second order factors (attention impulsiveness, motor and unplanned); (xi) Reflective Function Questionnaire **(RFQ)** [98, 99] consists of 8 items that classify hyper or hypo mentalization, in terms of the ability to interpret both self and others internal mental states such as feelings, desires, goals, desires and attitudes; only for AN (xii) Toronto Alexithymia scale **(TAS-20)** is a 20-question tool that is one of the most commonly used measures of alexithymia. People with alexithymia have trouble naming and describing their emotions, tend to downplay their emotional experiences and concentrate on the outside world.

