### Flexibility and Parkinson Disease

PD is a progressive neurodegenerative disorder that exhibits a gradual progression in function. It is characterized by the presence of misfolded α-synuclein protein aggregates in the brain, causing cell death primarily in the substantia nigra and other brain structures [41]. Traditionally, in clinical practice, PD is diagnosed based on the presence of cardinal motor symptoms, namely bradykinesia, resting tremor, and rigidity [42]. In addition to motor symptoms, PD has been documented to manifest rigidity in cognitive and personality domains as well [30, 43]. In the context of PD, individuals affected by this condition demonstrate a notable impairment in their capacity to adapt their current behaviors in order to align with the optimal response required by the surrounding environment. This cognitive ability, commonly referred to as cognitive flexibility, seems to be compromised in PD patients. For instance, Windmann and colleagues [44] hypothesized that impaired switching abilities could potentially be attributed to set-shifting impairments. This hypothesis suggests that the active disengagement from the dominant pattern may be mentally taxing for these individuals. Set-shifting, also referred to as cognitive flexibility, pertains to the ability to effectively adapt to changing environmental demands through the flexible transition between different rules, tasks, actions, and mental sets [26, 45]. Dopamine plays a crucial role in this context. The significance of dopamine in intricate cognitive processes has been widely acknowledged in the literature [28, 46]. The prefrontal cortex of the human brain exhibits a significant presence of dopamine receptors and receives substantial dopaminergic fiber inputs from other regions within the cerebral cortex. The data obtained from PD research indicates that there are early deficits in dopamine pathways caused by the initial degeneration of dopamine neurons in the substantia nigra and ventral tegmental area. As a result, the nigrostriatal dopamine circuitry is impacted by the disease, leading to subsequent damage to the mesocortical and mesolimbic pathways [47]. In this context, it is readily comprehensible to discern the related deficit of PD, which is linked to the role of dopamine and the anatomical structures in which dopamine is located. In fact, abilities traditionally dependent on the integrity of the prefrontal-striatal loops, have been shown to be particularly sensitive to dopamine activity [43]. The cognitive domains commonly affected in individuals with PD as a result of the dopaminergic deficit include working memory, set-shifting, planning, and selective attention. Moreover, researchers suggest dopamine modulates the ability to implement nonroutine schemata and update operations (flexibility processes) [48]. Recent studies also suggest alterations in cognition, are not independent of personality, and emotional disturbance. In particular, researchers provide evidence of a typical emotional and personality pattern of inflexibility, cautiousness, industriousness, and low impulsivity [49], considering that weak set-shifting or cognitive inflexibility results in rigid or perseverative thinking and behavior.

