### Rehabilitation

Between the assessment phases, participants will be allocated to a rehabilitation program. It will be different based on the group: 15 days for PD and 4 weeks for anorexia patients.

PD will participate in a daily rehabilitation program from Monday to Saturday including one hour of physical therapy each day. Patients will be guided by a physiotherapist as they complete exercises that improve gait speed, walking ability, and balance. Depending on the patient’s comorbidities, the additional two hours per day may involve one or more of the following activities: rehabilitation psychology, speech and swallow therapy, language therapy, cognition therapy, and therapies oriented toward daily function and community reintegration.

Instead, patients with AN will go through 4 weeks of rehabilitation based on refeeding in a medical setting. The refeeding program is implemented by a multidisciplinary team of doctors, dietitians, educators, and psychologists. The following criteria form the basis of the refeeding strategy: Higher calorie feeding is preferred in moderately malnourished patients with AN; meal-only approaches or combined nasogastric plus meal-feeding approaches are taken into consideration based on patient compliance; higher calorie refeeding strategies appear safe in severely malnourished patients with AN in the presence of medical monitoring and electrolyte correction.

As a crucial step in assisting the refeeding process, the rehabilitation psychology program will be coordinated and supervised by the psychologist with the aid of the educator, with daily individual meetings.

Patients who can support physical activity will go through a standardized rehabilitation program: during these 4 weeks, they will be directed by a physiotherapist through exercises to improve their walking ability and endurance, and balance control an hour a day, from Monday through Saturday. The proposed rehabilitation is an element of clinical routine, and we need to understand whether and how mental flexibility, encoded in its cognitive-affective dimensions, is a trait or state dimension. Patients, after routine rehabilitation performed in the hospital, might have an improvement in the affective-cognitive components of MF [53].

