**Fig 5 pone.0293921.g005:**
[figure not shown]
Markov chain model. From the Core affect model of Russel we can compute 12 complete transitions between affective states, we can insert them in a randomized sequence, calculate transition between blocks and state trait indexes, and once the variability indexes have been relativized, we can fit them into a Markov matrix.

By doing so, we effectively capture the probability of transitioning between and into blocks, empowering to uncover the intricacies of affect dynamics in both music’s auditory realm and images’ visual domain.

From each subject’s data and for each physiological signal, we extracted and analyzed only the main-diagonal indexes, denoted as state trait indexes (AA-BB-CC-DD), which convey the subject’s probability of remaining anchored in a specific affective state (stability).

This meticulous methodology allows us to rigorously assess and understand the dynamics of affective experiences through the lens of Markov chains, offering valuable insights into the temporal evolution of emotional states in our experimental context.

Our anticipated outcomes encompass the following hypotheses:

For participants within the control group, we hypothesize that there will be no statistically significant differences between the scores obtained at T0 and T1, both for measures of cognitive flexibility and affective flexibility. This expectation suggests that individuals in the control group are likely to maintain stable levels of cognitive and affective flexibility over time.Conversely, we expect an interaction effect between group membership (patients) and time (T0 to T1). This interaction effect signifies our hypothesis that cognitive flexibility measures will exhibit improvement over time among patients, leading to concurrent enhancements in affective flexibility. In particular, motor rehabilitation could have a significant impact on executive function, related to mental flexibility, while cognitive-behavioral therapy of individuals with AN could have an impact on both executive function and emotional flexibility.

In essence, our statistical analysis anticipates that patients will demonstrate increased cognitive and affective flexibility throughout the study period.

These hypotheses provide a clear framework for our statistical analysis and offer valuable insights into the expected outcomes of this multifaceted assessment of flexibility.

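### In Parkinson's patients the stated TMT score is completion time alone, so a gain in movement speed after rehabilitation could pass for better shifting

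*Protocol article*

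**What the plan says.** All references are to the protocol article.

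- **Assessment.** The neuropsychological battery is presented as a way to assess flexibility. On TMT-A and TMT-B: "The first is a searching task, the second requires shifting abilities". The one scoring rule given covers both parts: "The time used to perform each task is considered during the scoring: the highest the time the worst score". No score that corrects TMT-B for TMT-A is named.
- **Assessment, Tower of London (ToL).** "The ToL traditionally measures strategical reasoning, problem-solving, and mental planning", and "Time and accuracy are evaluated".
- **Flexibility and Parkinson Disease.** PD is diagnosed on "cardinal motor symptoms, namely bradykinesia, resting tremor, and rigidity".
- **Rehabilitation.** PD patients have an hour of physical therapy a day, Monday to Saturday: "Patients will be guided by a physiotherapist as they complete exercises that improve gait speed, walking ability, and balance". Two further hours a day may include cognition therapy, among other activities. No rehabilitation is described for controls.
- **Statistical analysis and Fig 4 caption.** Each measure of cognitive and affective flexibility goes into a group (patient or control) by time (T0 or T1) ANOVA. The composite cognitive flexibility score uses self-report data only.
- **Statistical analysis, hypotheses.** An interaction is expected, and "motor rehabilitation could have a significant impact on executive function, related to mental flexibility".

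**The concern.** Joining targets with a pen takes hand movement as well as search and shifting. In a disease marked by slow movement, TMT-B time mixes all three. The programme between the two assessments is partly motor, and it is given to the patients whose change is being tested. A motor gain would therefore occur in the patient arm only, and the control group could not subtract it. A patient who moves faster at T1 but shifts no better would still have a better TMT-B score.

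At stake is how a PD group by time interaction on TMT-B time would be read. The hypotheses credit motor rehabilitation with executive gains. On this measure, the stated score cannot tell that effect apart from a gain in movement speed.

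**Working it through.** **The plan's own figure.** The PD sample size calculation reproduces. With f = 0.39, two groups, two measurements, correlation 0.5 and N = 24, λ = f² × N × m / (1 − ρ) = 0.1521 × 24 × 2 / 0.5 = 14.6016. The critical F(1, 22) is 4.3009 and the power is 0.954. The article projects about 30 per group, and I use that below.

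**Inputs not in the document (assumptions).** TMT-A 60 s and TMT-B 150 s at T0; SD of the change in log time 0.20 to 0.25; motor speed gain 10 to 15% in patients and none in controls; no change in shifting.

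**Upper limit on the motor gain.** The Assessment section gives this instruction for the two parts: "connect the numbers from 1 to 25 in sequential order or numbers from 1 to 13 and letters from A to N in alternating order". Both therefore need a similar number of connections. The motor time in TMT-B is then about that in TMT-A, and it cannot exceed the whole of TMT-A. If all 60 s of TMT-A were motor time, a 10 to 15% gain would be 60 × 0.10 = 6 s to 60 × 0.15 = 9 s. On TMT-B that is 6/150 = 4% to 9/150 = 6%.

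**Spurious shift on TMT-B.** d = −ln(1 − gain/150) / SD:

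| Motor gain | SD of log change | d | False significance, 30 per group |
|---|---|---|---|
| 6 s | 0.25 | 0.0408/0.25 = 0.16 | 10% |
| 6 s | 0.20 | 0.0408/0.20 = 0.20 | 12% |
| 9 s | 0.25 | 0.0619/0.25 = 0.25 | 16% |
| 9 s | 0.20 | 0.0619/0.20 = 0.31 | 22% |

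The last column is the two-sided rejection rate at 0.05 from the noncentral t with 58 df and noncentrality d × √(30/2). If only 30 s of each part is motor time, the gain is 3 to 4.5 s and the rate is about 6 to 9%, close to nominal.

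**Which correction removes it.**

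- *Equal seconds off both parts (9 s).* B − A stays at 90 s: (150 − 9) − (60 − 9) = 90. B/A rises from 150/60 = 2.50 to 141/51 = 2.76, so motor recovery would look like worse flexibility.
- *Equal proportion off both parts (15%).* B/A stays at 2.50 (127.5/51). B − A falls from 90 to 76.5 s, a drop of 13.5 s.

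A simulation of the additive case agrees. It assumed 30 per group; motor time 30 s (SD 8), search 30 s (SD 6), shifting 60 s (SD 20); and occasion noise of 8 s (A) and 16 s (B). Its gains of 5, 8 and 12 s are 17 to 40% of the assumed motor time, larger than those above, so it serves to compare scores and not to size the problem.

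| Motor gain | TMT-B time | B − A | B/A |
|---|---|---|---|
| 5 s | 13% | 5% | 9% |
| 8 s | 27% | 5% | 19% |
| 12 s | 53% | 5% | 38% |

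**The case against.** - **The score may not be raw.** The article says that Italian-validated versions are used, and a full protocol or analysis plan may define a derived TMT score. Silence on B − A is not proof that it will not be used, and an article may leave that detail out. What stands is that the article does state a scoring rule, and that rule is time per part.
- **The hypothesis does not rest on TMT-B.** A reader might infer that motor recovery alone would confirm the PD hypothesis. The document does not support that. The composite is self-report only. The battery also has fluency tests scored by item counts (alternate fluency is itself described as a set-shifting test) and a card-sorting test judged on right or wrong placement. No passage lists TMT-B time as an ANOVA outcome by name; the Fig 4 caption implies it by covering each measure.
- **The motor route is inferred.** The named exercises target gait, walking and balance. A gain in hand speed is plausible but not stated. The optional cognition therapy means that a real change in shifting is possible too.
- **A larger effect is tempting.** Taking 10 to 15% off the whole TMT-B time gives 0.42 to 0.81 SD and 36 to 87% false significance at 30 per group. But 90 of the assumed 150 s is the excess of B over A, which is largely not motor. Cutting that part means faster shifting, not just faster movement.
- **ToL.** It is described as a planning test and is scored on accuracy as well, so only its time component is open to this problem.

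These points limit the size and reach of the concern. They do not remove the ambiguity in TMT-B time.

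**Conclusion.** The point holds in a limited form. As scored in the article, TMT-B time in PD cannot separate faster movement from better shifting, and the control group does not help because the motor programme is described for patients only. If TMT-B time is analysed as a flexibility measure, a motor gain could contribute to the interaction.

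With the assumed times and SDs, a motor-only gain of at most 6 to 9 s gives about 0.16 to 0.31 SD and 10 to 22% false significance at 30 per group, against 5%. The true size is unknown, because the document gives no test times, no variability and no expected hand-speed gain. This is an inexpensive improvement to one measure and one part of another. It does not undermine the PD hypothesis as a whole.

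**What to change.** For the PD group:

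1. Define the TMT flexibility score as TMT-B corrected for TMT-A. Use B minus A as the main score, since it cancels an equal gain in seconds, and log(B/A) as a sensitivity score, since it cancels a proportional gain.
2. Keep TMT-A time as a speed measure and report its T0 to T1 change beside the flexibility score.
3. Report ToL accuracy separately from ToL time.
4. State in advance that a fall in raw TMT-B or ToL time alone will not be read as improved flexibility.

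**Cost.** No extra data: both TMT parts and ToL accuracy are already collected. Derived scores are somewhat less reliable than raw times, and each removes the motor part fully only under its own assumption. If the two TMT scores disagree, the TMT result should be reported as unresolved.
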